#### 11.4.2 End of study treatment

Patients would stop treatments before the end (day 7 or 14) for the following reasons:

- Life-threatening SAE related to MaaT033
- Medical decision: for instance, disease progression due to treatment failure according to the investigator's judgement

Patients who stop treatments from the study for clinical / symptomatic deterioration or disease progression will continue to be monitored for safety follow-up, survival and disease until day 44. The reason for and the date of end of treatment must be documented.

If the treatment discontinuation is related to an AE, the subject will be followed up to recovery or stabilization of the AE, whichever comes last. All definitive treatment discontinuation should be recorded by the Investigator in the appropriate pages when considered as confirmed.

#### 11.4.3 Maintenance use

A total of 7 or 14 days of treatment are planned. However, the duration of treatment will depend on patient's tolerance.

### **11.5 PREMATURE DISCONTINUATION OF THE STUDY OR PREMATURE CLOSE-OUT OF A SITE**

#### 11.5.1 Decided by the Sponsor in the following cases:

The trial can be prematurely stopped (definitely or temporarily) when:

The treatment is considered as too noxious to continue with further clinical investigations

If the information on the product leads to doubt as to the benefit/risk ratio;

Occurrence of new fact that can modified modify MaaT Pharma / Competent Authority approval on the trial, or for any unethical reason

MaaT Pharma decision to stop product development

|                                                                                   |                    |                                                                      |
|-----------------------------------------------------------------------------------|--------------------|----------------------------------------------------------------------|
| [figure not shown] | DOCUMENT    | Protocol ID : MPOH05
EudraCT N° : 2019-004253-89
Version: 10.0 |
|                                                                                   | CIMON STUDY | Date : 04 MAY 2021
Page 42 / 70                                   |

In case of any reason motivating such withdrawal, the Investigator should promptly inform the patients, ensure appropriate therapy and follow-up, and complete the CRF with all available data at the time of trial arrest.

Trial withdrawal with the reason will be declared to Competent Authority (and EC if applicable) in accordance with local requirements.

If the Investigator has received from the Sponsor means and information necessary to perform the Clinical Trial and has not included any subject after a reasonable period of time mutually agreed upon;

In the event of breach by the Investigator of a fundamental obligation under this agreement, including but not limited to breach of the Clinical Trial Protocol, breach of the applicable laws and regulations or breach of the ICH guidelines for Good Clinical Practice;

If the total number of subjects are included earlier than expected;

In any case the Sponsor will notify the Investigator of its decision by written notice.

#### 11.5.2 Decided by the Investigator

The Investigator must notify (30 days' prior notice) the Sponsor of his/her decision and give the reason in writing.

In all cases (decided by the Sponsor or by the Investigator), the appropriate Ethics Committee(s) (IRB/IEC) and Health Authorities should be informed according to applicable regulatory requirements.

|                                                                                   |                    |                                                                      |
|-----------------------------------------------------------------------------------|--------------------|----------------------------------------------------------------------|
| [figure not shown] | DOCUMENT    | Protocol ID : MPOH05
EudraCT N° : 2019-004253-89
Version: 10.0 |
|                                                                                   | CIMON STUDY | Date : 04 MAY 2021
Page 43 / 70                                   |

## 12 **SAFETY**

All events will be managed and reported in compliance with all applicable regulations and included in the final Clinical Study Report.

When it is deemed necessary, the Investigator should consider reporting the cases and completing an SAE form and referring to an appropriate specialist to ensure proper characterization and documentation of the event as well as to ensure appropriate management.

### 12.1.1 **Definitions (ICH / GCP)**

An **Adverse Event** is any untoward medical occurrence in a subject or clinical investigation subject administered a pharmaceutical product and which does not necessarily have to have a causal relationship with this treatment.

A priori, efficacy endpoints as specified in the protocol will not be considered as AEs except if, because of the course or severity or any other features of such events, the Investigator, according to his/her best medical judgment, considers these events as exceptional in this medical condition.

If a subject is medicated or receives other non-study therapy for an abnormal Clinically Significant laboratory evaluation (unless this is standard of care or for a pre-existing condition), this will be recorded as an AE.

An **Adverse Drug Reaction** is any noxious and unintended response to a medicinal product related to any dose administered. The phrase response to a medicinal product means that a causal relationship between a medicinal product and an adverse event is at least a reasonable possibility, i.e. the relationship cannot be ruled out.

A **Serious Adverse Event** is any untoward medical occurrence that at any dose:

- 1 Results in death or;
- 2 Is life-threatening or;

Note: The term "life-threatening" in the definition of "serious" refers to an event in which the subject was at risk of death at the time of the event; it does not refer to an event which hypothetically might have caused death if it were more severe.

- 3 Requires subject hospitalization or prolongation of existing hospitalization or;

**Note: Planned hospitalization before inclusion and procedures related to AML or HR-MSD routine management will not be considered as SAE**

- 4 Results in persistent or significant disability/incapacity or;
- 5 Is a congenital anomaly/birth defect;
- 6 Is a medically important event:

Medical and scientific judgment should be exercised in deciding whether expedited reporting is appropriate in other situations, such as important medical events that may not be immediately life-threatening or result in death or hospitalization but may jeopardize the subject or may require intervention to prevent one of the other outcomes listed in the definition above.

|                                                                                   |                    |                                                                      |
|-----------------------------------------------------------------------------------|--------------------|----------------------------------------------------------------------|
| [figure not shown] | DOCUMENT    | Protocol ID : MPOH05
EudraCT N° : 2019-004253-89
Version: 10.0 |
|                                                                                   | CIMON STUDY | Date : 04 MAY 2021
Page 44 / 70                                   |

### **Unexpected Adverse Drug Reaction:**

An adverse reaction, the nature, or severity of which is not consistent with the applicable product information (e.g. Investigator's Brochure for an unapproved investigational product or package insert/summary of product characteristics for an approved product).

The Investigator should ensure that adequate medical care is provided to the subject for any adverse event.

#### **12.1.2 Collection, recording and reporting of adverse events**

In this study, all events have to be reported from V1 to V4 and a particular attention should be given to events related to infectious disorders. In case of sepsis that may be related to the IMP according to the investigator, any sample of interest must be collected and analyzed for the identification of the pathogen – according to the SOP “Sepsis” that MaaT Pharma has for these instances.

Following notification from the investigator, the Sponsor takes responsibility for reporting the suspected unexpected serious adverse reactions (SUSAR) and any follow-up information to EMA's EudraVigilance and local EU Health Authorities as necessary for the patient involved according to the required timelines.

In particular, the sponsor will inform the investigators of all sites of serious and unexpected adverse events that are considered to be possibly or probably related to the administered IMP.

All SAEs designed as “not related” to the IMP, will be reported to the authorities in Development Safety Update Report (DSUR) annually, if appropriate.

All COVID-19 infections must be reported as an SAE. The Sponsor takes responsibility for reporting this type of infection immediately to ANSM as a new fact.

Moreover, any other new information that might materially influence the benefit-risk assessment of the IMP or that would be sufficient to consider changes in IMP administration or in the overall conduct of the clinical study, must be reported to the authority.

In accordance with the ICH GCP guidelines, the sponsor will inform the investigators of findings that could affect adversely the safety of the subjects, impact the conduct of the study, or alter the authority approval to continue the study.

#### **12.1.3 Obligation of the Investigator regarding safety reporting**

##### **12.1.3.1 Adverse Events**

All Adverse Events regardless of seriousness or relationship to Investigational Product, spanning from the first visit planned in the Clinical Trial Protocol (V1), up to the last visit planned in the protocol (V4), are to be recorded on the corresponding page(s) included in the eCRF.

Whenever possible, symptoms should be grouped as a single syndrome or diagnosis. The Investigator should specify the date of onset, intensity (mild, moderate, severe), action taken with respect to Investigational Product, corrective treatment/therapy given, additional investigations performed, outcome and his/her opinion as to whether there is a reasonable possibility that the Adverse Event was caused by the Investigational Product.

|                                                                                   |                    |                                                                      |
|-----------------------------------------------------------------------------------|--------------------|----------------------------------------------------------------------|
| [figure not shown] | DOCUMENT    | Protocol ID : MPOH05
EudraCT N° : 2019-004253-89
Version: 10.0 |
|                                                                                   | CIMON STUDY | Date : 04 MAY 2021
Page 45 / 70                                   |

### **12.1.3.2 Serious Adverse Events**

In the case of a Serious Adverse Event the Investigator must immediately:

- 1 ENTER (within 24 hours) the information related to the Serious Adverse Event in the appropriate screens of the e-CRF; the system will automatically send the notification to the pharmacovigilance officer after approval of the Investigator within the e-CRF or after a standard delay. A back-up plan is in place (using paper flow) when the e-CRF system does not work,
- 2 In case of eCRF system failure, FILL in (within 24 hours) the information related to the Serious Adverse Event in the appropriate Serious Adverse Event Form and fax it immediately to the pharmacovigilance officer (Vigipharm subcontractor).
- 3 SEND (preferably by fax or e-mail) the photocopy of all examinations carried out and the dates on which these examinations were performed, to the pharmacovigilance officer.

Care should be taken to ensure that the subject's identity is protected and the subject's identifiers in the Clinical Trial are properly mentioned on any copy of source document provided to the Sponsor. For laboratory results, include the laboratory normal ranges.

All further data updates should be recorded in the eCRF as appropriate, and further documentation as well as additional information (for lab data, concomitant medication, subject status) should be sent (by fax or e-mail) to the Monitoring Team within 24 hours of knowledge. In addition, any effort should be made to further document each Serious Adverse Event that is fatal or life threatening within the week (7 days) following initial notification.

SAE EMAIL : [[contact]](mailto:[contact])

SAE FAX N° [contact]

The Investigator must comply with any applicable site-specific requirements related to the reporting of SAEs) involving his/her subjects to the Ethics Committee/Institutional Review Board (EC/IRB) that approved the trial.

Investigator should ensure that adequate medical care is provided to the subject for any adverse event.

All SAE must be followed until the subject has recovered, stabilized, recovered with sequelae or died. The Investigator must forward follow-up information on SAE to MaaT Pharma within 5 days this information is obtained. SAE Follow-up report should be faxed accordingly to SAE EMAIL: [[contact]](mailto:[contact]) and SAE FAX N° [contact]

### **12.1.3.3 Adverse Events of Special Interest**

The events of interest during MaaT033 treatment and follow up are AEs related to:

- Infections and infestations
- GI disorders

### **12.1.3.4 Laboratory tests abnormalities**

Any abnormal laboratory value should be reported as an AE, only if the following applies:

- If the abnormal value is associated with clinical symptoms, or
- If the abnormal value is considered medically significant by the Investigator, or
- If the abnormal value results in change of IMP administration (*i.e.* change in schedule, dose)
- If the abnormal value requires change in concomitant treatments or diagnostic evaluation to assess the risk for the patient.

|                                                                                   |                    |                                                                      |
|-----------------------------------------------------------------------------------|--------------------|----------------------------------------------------------------------|
| [figure not shown] | DOCUMENT    | Protocol ID : MPOH05
EudraCT N° : 2019-004253-89
Version: 10.0 |
|                                                                                   | CIMON STUDY | Date : 04 MAY 2021
Page 46 / 70                                   |

Any borderline value can be ultimately assessed by the PI to be on one or the other side of the corresponding threshold – taking a conservative approach and carefully considering the medical history and previous lab results of the patient.

### **12.1.3.5 Recording procedure**

Any event meeting the definition of an AE defined below must be collected and reported in the patient's CRF throughout study duration i.e., from the first trial related activity after the subject has signed the informed consent and until the end of the study.

All AEs must be followed until resolution or up to the end of the protocol. Serious adverse events that are life threatening, or leading to death, will be recorded throughout the study duration.

If there are several events and different symptoms combined into a main AE, then the only main AE (with a properly defined diagnosis according to code is always preferable) should be recorded in the CRF. Where there is no link between different clinical symptoms occurring at the same time, each sign should be recorded as a separate AE.

Occurrence and follow-up of AE should be assessed at each visit, and essential data listed hereafter should be recorded in the patient's CRF and patient's medical file as well:

- the severity or grade of the adverse event
- the causality: determination of whether an adverse event is reasonably related to the investigational treatment or procedure, and/or other agents are suspected of causing the adverse event
- the action(s) taken regarding investigational product (continued / interrupted / stopped)
- the corrective treatment if any
- the event outcome
- the seriousness of the event

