#### 8.2.2 **Decision rules for choice of dose regimen**

This study has for objective to assess MTD and MAD in term of MaaT033 activity (bacteria engraftment). Activity assessment requires a minimum of 6 patients to allow for a sufficient robust analysis of engraftment.

Activity and tolerability assessment may depend both on duration of treatment and/or daily dose. Therefore, the study will assess both 7 days and 14 days dose regimen, for the 3 capsules/day dosing.

Therefore, the study will ensure that a minimum of 6 patients is included for all the dose regimen that do not reach the MTD.

Definitions:

**Minimal Active Dose (MAD):** Minimum dose regimen that will lead to a minimal activity (1 or 2, cf chapter 8.3.2) of the product.

|                                                                                   |                    |                                                                      |
|-----------------------------------------------------------------------------------|--------------------|----------------------------------------------------------------------|
| [figure not shown] | DOCUMENT    | Protocol ID : MPOH05
EudraCT N° : 2019-004253-89
Version: 10.0 |
|                                                                                   | CIMON STUDY | Date : 04 MAY 2021
Page 24 / 70                                   |

**Dose Limiting Toxicity (DLT):** Toxicity event will be defined as any related adverse event grade >3 based on CTCAE v5.0 criteria for:

- Blood and lymphatic system disorders (DLT when grade4 or 5)
- Immune system disorders (DLT when grade4 or 5)

And any related adverse event grade  $\geq 3$  for all other system organ.

**Maximal Tolerated Dose (MTD):** Maximal dose for which only 0 or 1 patient do experience limiting toxicity out of a cohort of 6 patients.

The study has an adapted “6 dose titration” escalation design to allow for assessment of tolerability (research of the Maximal Tolerated Dose) and of activity (research of Minimal Active Dose):

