#### **12.1.4.1 Tolerability consideration:**

Investigators will be trained regarding the mode of action of the investigational medicinal product and to be particularly attentive to any signs of toxicity.

**Dose Limiting Toxicity (DLT):** Based on the literature and our preclinical data, no particular toxicity is expected. Toxicity events will be defined as any at least possibly related adverse event grade  $\geq 3$  based on CTCAE v5.0 criteria. Due to the specific therapeutic protocol that blood cancer patients usually follow, the follow-up of patients in term of DLT is set from V1 (end of neutropenia) to V3 (start of a new chemotherapy cycle, or consolidation). Nevertheless, there are some anatomical or physiological system events that will be considered as expected in the context of patients with AML or HR-MSD, and thus not related to the treatment. Such events will only be considered DLT when grade  $> 3$ :

- Blood and lymphatic system disorders (DLT when grade 4 or 5)
- Immune system disorders (DLT when grade 4 or 5)

Depending on the number of DLTs, the dose is either escalated (0 DLTs) or de-escalated ( $\geq 2$  DLTs). Due to our specific drug activity assessment goals, cohorts 2 to 5 will systematically be expanded with 3 extra patients (0 or 1 DLTs) each.

|                                                                                   |                    |                                                                      |
|-----------------------------------------------------------------------------------|--------------------|----------------------------------------------------------------------|
| [figure not shown] | DOCUMENT    | Protocol ID : MPOH05
EudraCT N° : 2019-004253-89
Version: 10.0 |
|                                                                                   | CIMON STUDY | Date : 04 MAY 2021
Page 49 / 70                                   |

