#### 14.1.1 **Endpoints**

Detailed definitions of endpoints are given in [section 8.3.1](#).

The primary evaluation criterion is the proportion of patients having experienced drug related adverse events for the determination of a recommended phase 2 dose (RP2D).

Secondary endpoints are:

- Evaluation of microbiota reconstitution post MaaT033
  - Alpha-diversity: Simpson index, Shannon index, Richness index
  - Similarities between samples: Bray-Curtis/Jaccard/UniFrac distances indexes, Sorensen index, Pearson index, Spearman index
- Duration of overall response on the hematologic malignancy (blasts)
- Compliance to allogeneic MaaT033 treatment
- Acceptability of MaaT033 by the patient
- Number of patients receiving the full treatments
- Evaluation of MaaT033 activity and/or impact on:
  - Number and percentage of patients having experienced at least one infection requiring antibiotic/antiviral/antifungal therapy after MaaT033 treatment start
  - Number and percentage of patients having experienced at least one microbiologically documented infection requiring antibiotic/antiviral/antifungal therapy after MaaT033 treatment start
  - Events potentially related to GI infection (fever, diarrhea, abdominal pain, bloating)
  - Fecal resistome and MDRB carriage
  - Evaluation of stools: Bristol stool chart

Exploratory endpoints encompass

- Assessment of a microbiota signature
- Impact of MaaT033 on the immune system

The final main analysis will be performed when all enrolled patients have completed treatment and follow-up period (28 days). Complementary analysis on safety and 12 months' survival follow up will be updated when all patients have had the opportunity to be followed for 12 months.

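### Recording only the main AE when linked events are combined can leave a related grade 3 infection or GI event uncounted as a DLT, because the DLT threshold depends on organ class

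*Protocol*

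**What the plan says.** Two parts of the protocol meet here.

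**Recording.** Section 12.1.3.5: "If there are several events and different symptoms combined into a main AE, then the only main AE" goes in the CRF, preferably as a defined diagnosis. Separate entry is required only for unlinked symptoms: "Where there is no link between different clinical symptoms occurring at the same time, each sign should be recorded as a separate AE". The same section has grade, causality, action taken, treatment, outcome and seriousness recorded for each AE. Section 12.1.3.1 adds a milder instruction about symptoms only: "Whenever possible, symptoms should be grouped as a single syndrome or diagnosis".

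**DLT definition.** Section 8.2.2 counts a related event only at grade 4 or 5 in two classes, "Blood and lymphatic system disorders (DLT when grade4 or 5") and "Immune system disorders (DLT when grade4 or 5"), and at grade 3 or more "for all other system organ". Section 12.1.4.1 repeats the split and gives the reason: "there are some anatomical or physiological system events that will be considered as expected in the context of patients with AML or HR-MSD", and are therefore taken as not related to treatment.

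Infections and GI disorders, which section 12.1.3.3 names as the events of special interest, fall under the grade 3 threshold.

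**The concern.** The merging rule covers events as well as symptoms, and it does not say how the main AE is chosen. Where linked events lie on both sides of the class split, the choice of main term can decide whether a grade 3 episode meets the DLT definition as recorded.

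Such mixed episodes are plausible. Patients enter once the neutrophil count reaches 0.5 x 10^9/L (section 8.2.1), so infection and low counts may well occur together. The study is open-label, so the main term is chosen with the regimen known.

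The stake is the escalation decision. At dose levels 2 to 5, zero or one patient with a DLT among six passes the level and two or more does not (section 8.2.2). A single uncounted patient can change the outcome.

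**Working it through.** **1. Reading the sections together.** Take a patient with a related grade 3 infection linked to a grade 3 fall in blood counts.

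- Recorded as two AEs: the infection is grade 3 in a grade 3-threshold class, so it is a DLT.
- Recorded once, with the infection as main AE: a DLT.
- Recorded once, with a grade 3 blood diagnosis as main AE: the entry is below its threshold of grade 4. The infection has no grade or causality entry of its own, and the entry sits in a class that section 12.1.4.1 presumes expected and unrelated.

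No section exempts infections or GI disorders from merging. None has merged components assessed separately for DLT.

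**2. Size, as an illustration.** The protocol states no target DLT rate and no operating characteristics, so there is no figure of its own to reproduce. Inputs:

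- n = 6 and the pass rule of 0 or 1 patient with a DLT, from section 8.2.2;
- p, the true DLT probability: assumed;
- m, the share of DLTs lost through merging after any recovery by the committee: assumed, since the document gives none.

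The counted rate is q = p(1 - m), and P(pass) = (1 - q)^6 + 6q(1 - q)^5.

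For p = 0.30:

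- m = 0, q = 0.30: 0.1176 + 0.3025 = 0.420
- m = 1/4, q = 0.225: 0.2167 + 0.3774 = 0.594
- m = 1/3, q = 0.20: 0.2621 + 0.3932 = 0.655

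Over a wider range of assumptions, P(pass) is:

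| p | m = 0 | m = 10% | m = 25% | m = 50% |
|---|---|---|---|---|
| 0.10 | 0.886 | 0.905 | 0.931 | 0.967 |
| 0.20 | 0.655 | 0.704 | 0.776 | 0.886 |
| 0.33 | 0.358 | 0.427 | 0.540 | 0.741 |
| 0.50 | 0.109 | 0.164 | 0.274 | 0.534 |

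**3. The decisive case.** In a cohort with exactly two true DLT patients, losing one changes the outcome from fail to pass. With independent losses the chance of losing at least one is 1 - (1 - m)^2: 0.19, 0.44 and 0.75 for m = 10%, 25% and 50%.

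**The case against.** The case against is substantial.

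- **The DLT call is not tied to the CRF term.** Sections 8.2.2 and 12.1.4.1 define a DLT on the adverse event, its grade and its organ system. A reader might infer that a merged grade 3 infection automatically ceases to be a DLT. The text does not say that; the event can only go uncounted if the assessment follows the recorded entry.
- **There are safeguards.** Three physicians review every case profile (8.3), the committee referees causality (12.1.4), and the cohort meeting must make sure all DLTs are found (12.1.4.2). Culture results go into the eCRF (11.1.2, 11.3.1), SAE reports come with copies of examinations (12.1.3.2), and infections get particular attention (12.1.2). These should recover some cases. They give no rule for splitting a merged AE, however, so recovery depends on the committee noticing the component.
- **An infection is at least as natural a main diagnosis.** Nothing tells investigators to file infections under blood or immune terms. This stands, and it limits how often the problem arises.
- **Losses need not run one way.** A reader might infer that merging can only lower the DLT count. The protocol does not say how a merged AE is graded. A grade 2 infection and a grade 3 blood event, neither a DLT alone, could become one grade 3 infection and count.
- **The GI symptom endpoint.** A reader might also infer that merging strips fever, diarrhea, abdominal pain and bloating from the endpoint in section 14.1.1. Table 1 has these symptoms collected daily from V1 to V4 apart from AE entry, so that does not follow.
- **The rates are assumed and toxicity is expected to be low.** Section 12.1.4.1 expects no particular toxicity, and section 6.4 shows 1 related SAE among 81 patients on related products. At a 10% DLT rate, a one-third loss moves P(pass) only from 0.886 to 0.944 (q = 0.10 x 2/3 = 0.067).

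Grouping symptoms into a diagnosis is ordinary practice, and the higher blood and immune threshold is a deliberate choice; neither is criticised here.

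**Conclusion.** The point holds in a conditional form. The recording rule in 12.1.3.5 and the class-dependent DLT threshold do not fit together where linked events cross classes. A related grade 3 infection or GI event recorded only under a grade 3 blood or immune diagnosis can go uncounted unless the committee recovers it from the case profile.

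The frequency cannot be determined from the protocol. The rise from 0.42 to 0.59 or 0.66 rests on an assumed 30% DLT rate and assumed losses of one quarter or one third, so it shows sensitivity and is not an estimate. What does not depend on those rates is that one uncounted patient can turn a failed six-patient cohort into a passed one. Because the correction is cheap, it is worth making.

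**What to change.** Keep diagnosis grouping for symptoms and for grade 1-2 components. Add to section 12.1.3.5, with a matching line in 12.1.3.1, that any component event of grade 3 or more, in particular an infection or GI disorder, is recorded and graded as its own AE and linked to the main diagnosis. Add that the committee judges each such component for DLT under its own organ class and counts patients, not events, so that one episode is not counted twice. There is no need to split out every infection or GI event regardless of grade. The DLT thresholds and escalation rules stay as they are.

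The cost is protocol and eCRF-guideline wording, a few more AE lines, and some linked duplicates in the AE tables.
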